### Comparison to Previous Work

This RCT assesses the impact of 2 interventions—the provision of free hearing aids and an HHE program on social connections and functioning among community-dwelling Chinese adults with HI. The design of this RCT is partly similar to the Aging and Cognitive Health Evaluation in Elders (ACHIEVE) RCT conducted in the United States, which commenced in 2017. The ACHIEVE trial implemented a 3-year hearing intervention that included audiological counseling and provision of hearing aids, alongside a control intervention on successful aging health education. A notable distinction in our study’s design is the inclusion of a control group that receives no intervention, as well as the specificity of our health education to hearing-related topics. While the ACHIEVE trial primarily targeted cognitive outcomes, it also assessed some mental health and well-being outcomes [54]. In contrast, our study is specifically oriented towards social functioning. Furthermore, secondary analysis of ACHIEVE data indicated no significant association between the 3-year interventions—either hearing aid provision or health education—and health-related quality of life [55]. Our research will help examine the effectiveness of these interventions among older adults with HI within a different sociocultural context. Our use of WHO-DAS II as a generic measure in the hearing-impaired population is similar to another 12-month hearing aid intervention research conducted in the United States [23].

Currently, among the completed RCTs concerning community hearing intervention rehabilitation in China, 2 studies exhibit similarities to our community interventions. One of these studies conducted a 20-month hearing aid intervention [51], while the other implemented a 3-month hearing aid combined with a health education intervention [56]. Both studies used a 2-arm design and assessed a range of outcome variables, with secondary outcomes including quality of life and social isolation. Our intervention design is characterized by a more complex 3-arm intervention design and a larger sample size, which is anticipated to yield more robust evidence regarding the long-term effects of hearing interventions. To our knowledge, this will be the first RCT to evaluate the efficacy of community-delivered hearing rehabilitative and supportive interventions—both hearing aids and health education—on older adults’ SWB in the context of Chinese aging society.

### Strengths

This study highlights 2 main strengths. First, the study makes a theoretical contribution by integrating the WHO’s ICF and IPC-EHC frameworks in conjunction with the stress process model. The WHO frameworks facilitate a focus on both individual and environmental factors in the design of interventions, emphasizing social isolation and functional outcomes, which distinguishes this research from traditional studies that primarily address quality of life and cognitive functions. Within the context of the stress process model, hearing deterioration is conceptualized as a chronic stressor that can have both direct and indirect effects on psychosocial distress [57]. Thus, the psychological pathway outlined in our hearing intervention aims to provide empirical support for the application of the stress model in the management of chronic diseases such as hearing loss, offering a detailed explanation of the role of stress within the model in relation to different health consequences.

Second, the interventions are community-oriented, which aligns with China’s policy setting on hearing rehabilitation and health promotion. Currently, China’s Action for Promoting Hearing Health in the Elderly mainly conducts activities based on communities, such as popularizing knowledge about hearing health, screening, and public health initiatives. Besides, both online and offline elements are blended in the interventions, which provides more convenient and efficient support and meets with current digital health trends. The findings of this study may provide valuable insights for health care and social workers to enhance well-being among older adults through auditory interventions.

### Limitations

Despite these strengths, the trial faces several limitations. First, the design of a one-time follow-up study presents challenges in evaluating the short-term effects of interventions, as well as their impacts beyond a 24-month period. The duration of intervention and follow-up is selected based on the following considerations: (1) previous research has consistently shown significant findings regarding the short-term effects of hearing aid interventions; however, the medium- to long-term effects remain ambiguous, and adherence to the prolonged use of hearing aids is notably low. Our primary interest lies in investigating these medium- to long-term effects; (2) given that the measurement tools used in both the baseline and follow-up questionnaires are fixed, we intend to extend the interval between the 2 measurements to mitigate potential learning effects; and (3) in addition, the constraints imposed by the project’s duration and funding are considered.

Second, there is a lack of subjective measures in our survey questionnaire. To address this gap, we conducted qualitative interviews after the RCT. A subset of older adults with HI from intervention groups were inquired about their satisfaction with the use of hearing aids, their experience in health education activities, and their assessments of the health education materials. In addition, we gathered feedback from CPs.

Third, the provision of free hearing aids may raise concerns regarding the social approval effect. Previous research on hearing aid interventions has typically involved the distribution of free devices [51,58,59]. In instances where there is a financial burden associated with acquiring commercial hearing aids, selection bias may arise, as economically disadvantaged older individuals may find it more challenging to participate in such interventions. The Chinese government has established a range of welfare policies aimed at supporting individuals with disabilities and the elderly, which include not only rehabilitation services, but also living subsidies for disabled individuals, long-term care insurance, and older adult care subsidies. Within this welfare framework, hearing aids do not represent a unique benefit. Therefore, we contend that the social approval effect remains within a manageable scope and is unlikely to compromise the reliability and validity of the RCT. Future research could also compare the intervention effects of paid hearing aids with those of free hearing aids.

Fourth, the interventions are conducted at different sites, which may result in geographical and selection biases. Nevertheless, the comparable socioeconomic and cultural contexts of these sites are expected to alleviate such biases. There was no pilot study due to time and budget constraints; however, given that the social and demographic characteristics of the feasibility study site closely resemble those of the formal trial sites, we believe this limitation does not pose a significant threat to the research design.

Fifth, our reliance on self-reported measures of social isolation and functioning may introduce measurement bias, which we will address through the use of validated tools, cross-validation, and multisource evaluations.

Lastly, although the sample size was determined using standard calculation methods, it remains relatively small, which affects its representativeness and external validity. Randomization in a small sample may not completely eliminate the preexisting differences either. Therefore, we will further use matching techniques or other econometric methods during the statistical analyses.

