### Conceptual Framework and Interventions

Both the ICF and stress-buffering models provide insights into how adult-onset HI affects SWB and the effectiveness of auditory interventions. The ICF describes the bidirectional association among impairments, activity limitations, and participation restrictions. Besides, functioning can be viewed as the outcome of interactions between health conditions and contextual factors, which include external environmental factors (eg, supportive environment or social attitudes) and internal personal factors (eg, coping style and psychological resources) [16]. The ICF reveals that the ideal interventions should consider a holistic approach combining physical, personal, and environmental factors. The stress-buffering model, derived from the stress process paradigm, posits that social and coping resources can buffer (mediate or moderate) the impacts of stressors such as HI on health and well-being by altering one’s appraisal and coping behaviors toward a stressor or threat [28,29]. Empirical studies support the potential psychological resilience to mediate the relationship between functional HI and SWB [14].

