### Study Design and Setting

A three-arm, single-blinded RCT with a 24-month follow-up period will be conducted. A total of 435 eligible participants were randomly assigned in a 1:1:1 ratio to a control group, a hearing aid use (HAU) group, or an HHE group. The HAU group will receive hearing aids and follow-up instructions. Due to budget constraints, the audiological rehabilitation intervention predominantly used hearing aids provided by the Audiology Department of the Guangdong Provincial Cultural Sports and Rehabilitation Assistive Devices Center for People with Disabilities (GPSRC), which is affiliated with the China Disabled Persons’ Federation (CDPF). Individuals diagnosed with disabling HI and classified as persons with hearing disability are eligible to apply for complimentary hearing aids and fitting services from the local CDPF departments. Since the number of adults with HI who were eligible for hearing-aid fitting was limited to one site at the time of the baseline survey and intervention, a total of 139 persons with disabled HI were randomly selected from 4 sites with similar socioeconomic and cultural conditions. The selection was based on the list provided by GPSRC, which maintains records of hearing-disabled persons in Guangdong Province. The HHE group will undergo both offline and online educational interventions, while no interventions are planned for the control group that is similar to a natural setting. A sample of 278 adults diagnosed with some degree of HI was randomly selected and assigned to the HHE group and control group from Hualong County in Guangzhou, Guangdong, based on its roster. For the HAU group, participants were prescribed hearing aids at baseline (T0) and received reinstruction on the use of hearing aids 12 months after T0. For the HHE group, participants were required to participate in an offline hearing education at T0, followed by an online educational intervention at 6 months after T0, and an offline information intervention at 12 months after T0. The primary outcomes are social isolation and functioning, assessed at baseline and 24 months.

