Allocation										✓	✓		✓																			
Interventions																																
Hearing aids provision										✓											✓						✓					
Hearing health education											✓						✓							✓						✓		
Assessments																																
Sociodemographics										✓	✓		✓														✓			✓		✓
Hearing outcomes																																
Pure-tone audiometry										✓	✓		✓																			
HHIA^d^ score										✓	✓		✓														✓			✓		✓
Self-reported hearing										✓	✓		✓														✓			✓		✓
IOI-HA^e^ score																											✓					
Hearing-related health literary										✓	✓		✓														✓			✓		✓
Communication ability											✓		✓														✓			✓		✓
SWB^f^ (primary outcome)																																
LSNS-6^g^ score										✓	✓		✓		✓												✓			✓		✓
WHODAS 2.0^h^ score										✓	✓		✓		✓												✓			✓		✓
ISE^i^ score										✓	✓		✓		✓												✓			✓		✓
SEAQ^j^ score										✓	✓		✓		✓												✓			✓		✓
Secondary outcomes																																
GSE^k^ score										✓	✓		✓														✓			✓		✓
PMS^l^ score										✓	✓		✓														✓			✓		✓
CD-RISC^m^ score										✓	✓		✓														✓			✓		✓
EQ-5D-5L score										✓	✓		✓														✓			✓		✓
SWLS^n^ score										✓	✓		✓														✓			✓		✓
Covariates										✓	✓		✓														✓			✓		✓
Lifestyle behaviors										✓	✓		✓														✓			✓		✓
Chronic diseases										✓	✓		✓														✓			✓		✓

^a^T: hearing aid intervention group.

^b^T: hearing health education intervention group.

^c^C: control group.

^d^HHIA: Hearing Handicap Inventory Screening Questionnaire for Adults.

^e^IOI-HA: International Outcome Inventory for Hearing Aids.

^f^SWB: social well-being.

^g^LSNS-6: Lubben Social Network Scale.

^h^WHODAS 2.0: World Health Organization Disability Assessment Schedule 2.0.

^i^ISE: Index of Social Engagement.

^j^SEAQ: Social Engagement and Activities Questionnaire.

^k^GSE: General Self-Efficacy Scale.

^l^PMS: Pearlin Mastery Scale.

^m^CD-RISC: Connor-Davidson Resilience Scale.

^n^SWLS: Satisfaction with Life Scale.

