**Secondary outcomes**

**
*Hearing health outcomes*
**
Hearing handicap is measured by the Hearing Handicap Inventory Screening Questionnaire for Adults (HHIA). Participants’ self-reported hearing status is also collected to reflect subjective hearing impairment (HI). For the hearing aid use (HAU) group, the International Outcome Inventory for Hearing Aids (IOI-HA) will be used during the follow-up period to verify the treatment effects of HAU.Hearing-related health literacy is measured through a set of 9 questions developed by the research team based on the Knowledge, Attitude, and Practice theory. The 9-item assessment evaluates the respondents’ understanding (eg, information on hearing health, preventive measures, and awareness of available hearing health care), attitudes (eg, beliefs and attitudes toward hearing health care, willingness to prioritize and engage in hearing health activities), and behaviors (eg, regular hearing check-ups, protection from loud noises, the use of hearing aids if needed) related to hearing health [44]. The content and validity of the 9-item questionnaire were evaluated by 5 experts in hearing and health education.Communication ability is measured in the follow-up survey using the 10-item Self-Assessment of Communication (SAC), a self-report questionnaire designed to assess the impact of hearing loss and hearing intervention outcomes [45].
**
*Psychosocial and health-related outcomes*
**
Self-efficacy is assessed by the 10-item Chinese version of the General Self-Efficacy Scale (GSE). It has been identified as a good tool for measuring self-efficacy in community-dwelling adults [46].A sense of mastery is measured by the 7-item Chinese version Pearlin Mastery Scale (PMS). In addition to self-efficacy, mastery serves as another psychological resource that may help mitigate the impact of stressors on well-being. PMS has been regarded as a well-validated measure commonly used in studies to examine adults’ health and well-being outcomes [47].Psychological resilience in the HHE group is evaluated using the 2-item Connor-Davidson Resilience Scale (CD-RISC). The 2-item CD-RISC has demonstrated good validity and reliability in the elderly or Chinese general population [48].Quality of life includes both a subjective and an objective measure. Health-related quality of life is measured by standard tests such as the EQ-5D-5L, and subjective well-being is measured by the 5-item Chinese version of the Satisfaction with Life Scale (SWLS).

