### Statistical Analysis

The intent-to-treat principle will be used during the impact analysis. The differences between the control and intervention groups in terms of primary and secondary outcomes will be evaluated through ANOVA and linear mixed-effects modeling. Multiple methods such as weighting, matching, and imputation will be used to handle the problem of missing data and sample attrition. In addition, a nonparametric bias-corrected case resampling bootstrap method, structural equation modeling, or interaction analysis will be used to further explore the buffering effect of psychosocial factors. Heterogeneity analysis will be applied to investigate whether the intervention effects are robust across subgroup samples, such as participants with different levels of objective hearing loss.

The cost-effectiveness analysis will be based on the costs of the HAU or HHE interventions and their effects on improving health-related quality of life, as measured by EQ-5D-5L. EQ-5D-5L is designed to measure the generic quality of life in terms of mobility, self-care, usual activities, pain or discomfort, and anxiety or depression [49]. Previous literature has used this multidimensional construct of quality of life to evaluate the effect of hearing interventions [50-53].

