## Discussion

### Principal Findings

We anticipate a significant positive effect of interventions on reducing social isolation and enhancing functioning outcomes, along with several psychological pathways, which contribute to these main results.

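### Mediators are first re-measured at the same 24-month visit as the outcomes, so the planned bootstrap/SEM analysis cannot establish the direction of any psychological pathway

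*Protocol article*

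**What the plan says.** **Timing.** Study Design and Setting states: "The primary outcomes are social isolation and functioning, assessed at baseline and 24 months". Limitations confirms two waves ("we intend to extend the interval between the 2 measurements to mitigate potential learning effects") and concedes that "the design of a one-time follow-up study presents challenges in evaluating the short-term effects of interventions", adding only that effects beyond 24 months are also out of reach. In Table 1 the rows for GSE, PMS and CD-RISC are ticked at day 0 and 24 months, with nothing at 6 or 12 months.

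**Analysis.** Statistical Analysis lists a "nonparametric bias-corrected case resampling bootstrap method, structural equation modeling, or interaction analysis" for exploring the buffering effect of psychosocial factors. Conceptual Framework and Interventions defines buffering as covering both mediation and moderation.

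**Intended conclusion.** Study Aims and Hypotheses raises psychological well-being as a possible pathway. Principal Findings goes further, expecting effects on isolation and functioning "along with several psychological pathways, which contribute to these main results". Strengths presents the pathway as empirical support for the stress model.

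**Two internal conflicts bear on this.**
- Table 1 has a 6-month tick for LSNS-6, WHODAS 2.0, ISE and SEAQ which, by column position, falls in the hearing-aid arm only. This does not agree with the two-wave design in Study Design and Setting and in Limitations.
- The secondary outcomes text says "Psychological resilience in the HHE group is evaluated using the 2-item Connor-Davidson Resilience Scale (CD-RISC"), whereas Table 1 ticks CD-RISC in all three arms.

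**The concern.** Random allocation protects the arm-to-mediator and arm-to-outcome contrasts. It does not protect the mediator-to-outcome link, which remains an observational association. To read that link as a pathway, the change in the mediator must at least come before the change in the outcome. Here both changes are seen for the first time at one interview, 24 months after baseline.

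The reverse order is plausible: a person who regains social contact may then report more self-efficacy, mastery or resilience. A third factor could also move both. In either case a product-of-coefficients analysis can return an indirect effect whose interval excludes zero although the mediator does nothing to the outcome. The trial would then report evidence for the stress-buffering model that its data cannot supply.

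**Working it through.** **1. The plan's own figure.** Inputs from Sample Size Calculation and Recruitment: d = 0.404, 85% power, 5% significance (sidedness not stated; two-sided assumed).

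n per arm = 2(1.960 + 1.036)² / 0.404² = 17.96 / 0.1632 ≈ 110.0, rounded up to 111, or 222 for two arms. This reproduces the stated figure; power at 111 per arm is 0.850 by the noncentral t. Allowing 20% loss, 111 / 0.80 = 138.75, or 139 per arm. The enrolled hearing-aid and control arms average (121 + 156) / 2 = 138.5. The illustration uses 140 per arm.

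**2. Model fit cannot choose the direction.** Arm T, mediator M and outcome Y supply 3 variances and 3 covariances, 6 moments in all. The model T→M→Y with a direct T→Y path has 3 paths and 3 variances, 6 parameters. The model T→Y→M with a direct T→M path also has 6. Both are just-identified and reproduce the same covariances exactly.

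**3. Apparent mediation when there is none.** Assume pure reversal:
- Y = 0.404·T + e
- M = r·Y + √(1 − r²)·e₂, so M has no effect on Y and the within-arm correlation is r.

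Then a (T→M) = 0.404·r and b (M→Y given T) = r, so a·b / 0.404 = r². The apparent share mediated is 4%, 9%, 16%, 25% and 36% for r = 0.2, 0.3, 0.4, 0.5 and 0.6.

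**4. How often it is declared significant.** Same model, 140 per arm, 95% bootstrap interval excluding zero. Ranges come from separate simulation runs. Simulation error at 600 trials is at most √(0.25/600) ≈ 2 percentage points.

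| Assumed r | Percentile bootstrap | Bias-corrected bootstrap |
|---|---|---|
| 0 | under 1% | – |
| 0.1 | about 2% | 4% |
| 0.2 | about 10% | 15% |
| 0.3 | 18–20% | 18–22% |
| 0.4 | 27–30% | 28–32% |
| 0.5 | 39–42% | 41–44% |
| 0.6 | 53–56% | 55% |

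The rate at r = 0 shows that the excess comes from the reversed order and not from the test. The bias-corrected interval, which the protocol names, does no better.

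**5. Does baseline adjustment repair it?** Pure reversal was simulated again with both baseline scores in the model and a Monte Carlo interval for a·b. For assumed outcome-to-mediator coefficients of 0.2, 0.3, 0.4 and 0.5:
- at 111 per arm, false pathways in 6%, 21%, 31% and 49% of trials;
- at 139 per arm, 10%, 24%, 38% and 61%;
- with an added interim wave of both mediator and outcome, 0.3% to 1.3% at 111 per arm.

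The missing element is the interim measurement, not the covariate set.

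**6. Shared cause.** Suppose the arm shifts M by an assumed 0.3 SD and Y by 0.404 SD separately, with residual correlation 0.2 to 0.5 from an unmeasured cause. At 111 per arm a false indirect effect appears in 50% to 60% of trials, against 3% at correlation 0.

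**7. Does the 6-month tick help?** No. No mediator is ticked at 6 months, and by column position neither the control arm nor the education arm has the social scales then.

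**The case against.** The strongest reply is that the protocol is already cautious. Study Aims and Hypotheses asks whether psychosocial factors buffer, and Outcome Measures and Statistical Analysis both speak of exploring. The article names families of methods only, so baseline adjustment or reversed models could properly sit in a fuller document. The simulated rates need a real 0.404 SD effect, wholly reversed causation and a correlation that the protocol does not give; at r = 0.1 the percentile rate is about 2%.

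Much of this stands, and it rules out several stronger readings that a reader might infer:
- *That the trial sets out to prove a causal pathway.* Its aims and analysis sections do not say so. The firmer language is confined to Principal Findings and Strengths.
- *That the protocol itself concedes reverse causation.* The sentence "The ICF describes the bidirectional association among impairments, activity limitations, and participation restrictions" concerns those three constructs. It says nothing about self-efficacy, mastery or resilience against LSNS-6 or WHODAS 2.0, and should not be cited for this point.
- *That the list joined by 'or' confuses mediation with moderation.* It follows the protocol's two-sided definition of buffering. Moderation by baseline level has the right time order and is not in doubt.
- *That outcomes too are measured at two times only.* The text says so, but Table 1's 6-month tick does not agree.

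The reply does not remove the core. Measurement times are fixed here and follow-up is complete (Trial Status), so no analysis plan can restore the order of treatment-induced changes. Baseline scores allow only a limited cross-lagged look. None of the listed limitations mentions the order of mediator and outcome.

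**Conclusion.** The point holds for the mediation reading only. With mediators at day 0 and 24 months, the planned bootstrap/SEM analysis can describe an association between arm, mediator and outcome but cannot support a direction. The expectations in Principal Findings and Strengths go beyond what the schedule can deliver.

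The illustrated rates, roughly 10% at r = 0.2 to about 55% at r = 0.6 with 140 per arm, assume a 0.404 SD outcome effect and a mediator that is purely a consequence of the outcome. They show what could happen and are not an estimate for this trial. The identification argument in step 2 needs no assumed correlation.

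A reader might extend the criticism to the main results. The documents do not support that: the primary treatment comparisons do not use the mediators, and this point leaves them untouched.

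**What to change.** In Statistical Analysis, replace the open list with two separate analyses:

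1. **Moderation.** Arm-by-baseline interactions with baseline GSE and PMS, and with baseline CD-RISC if it was measured in both arms compared. The secondary outcomes text and Table 1 must first be reconciled on who received CD-RISC; if only the education arm did, no between-arm resilience analysis is possible.
2. **Mediation.** The 24-month bootstrap/SEM model, adjusted for baseline mediator and outcome and labelled exploratory and associational. Report it beside the reversed-order model and a sensitivity analysis for unmeasured mediator-outcome confounding. Draw no directional conclusion whatever the fit, since both orderings fit equally.

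Reword Principal Findings and Strengths so that they no longer anticipate pathways or support for the stress model from concurrent data. Add the time-order limit to Limitations. Reconcile the 6-month tick in Table 1 with the two-wave design described in the text.

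The cost is wording, one additional model and one sensitivity analysis on data already collected. Trial Status says the intervention effects were still unknown at this protocol version, so the change could be made before results are seen. The price is a weaker mechanistic claim.
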